#### Statistics

All analyses will be focused at the patient level (inference unit will be patient). We will perform a series of frequency analyses tabulating outcome variables against various explanatory variables and/or confounders. Suitable descriptive statistics will be used. Since individual observations within the same cluster (ie. patients of one GP) may be correlated, the intra-cluster (intra-class) correlation coefficient (ICC) measuring such a “clustering effect” and estimating the relative variability within and between clusters will be calculated for both intervention- and control groups. Analysis of differences between BI- and BAU groups based on mixed linear models (MLM) will be performed to account for the hierarchical nature of data, where the main point is to allow variation to be modelled at each level of the data, for example, the GP and the patient level. 95% confidence intervals will be used.

Analysis based on prespecified hypotheses regarding the two primary and the secondary outcomes will be performed as hypothesis testing on the entire dataset and Bonferroni corrections will be used for multiple comparisons. For evaluation of possible outcome predictors where no prior data from this population exist, split file analysis 
[103] will be used. The splitting of the data set will be performed prior to any analyses of primary and/or secondary outcomes.

The intention-to-treat principle will be followed by including all patients with at least one follow-up response. Missing values will be handled using multiple imputation techniques.

SPSS 16.0 and SAS will be used for statistical analyses.

Registration of electronic data from the semi-structured interviews will be done by using Snap Survey (Snap Survey, London, UK).

The participating patients will receive a weekly reminder regarding the headache diary via mobile phone (SMS) during each two weeks diary period at three, six and twelve months, respectively.

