[30,35,64]. In addition, the SDS score has been shown to predict likelihood of successful detoxification in a general population 
[65].

Screening and Brief Intervention (BI) is a well-known approach to identify and treat unhealthy alcohol use 
[66]. The SDS and similar scales such as the Alcohol Use Disorders Identification test, have previously been used to identify individuals at risk for addiction-related problems 
[58-63,67-69]. BI involves the use of such an identification tool followed by feedback to the identified individual as being “at risk”. The final step, in this very short and simple intervention is to give information suggesting to cut down the use of the particular substance to predecided “acceptable” levels 
[66]. BI includes clear directive advice, but focus is also on increasing patients insight and awareness regarding overuse as described in more detail elsewhere 
[66,70]. The BI method has shown promising results with both short- and longlasting reduction of alcohol intake and levels of related biochemical markers such as liver transferase levels 
[66,71-73]. Similar methods have also been successfully applied for various other addictive drugs 
[70,74,75].

We have previously reported data from an open, un-controlled study of medication overuse headache in the general population, which suggested that three out of four MOH subjects had managed to reduce their medication intake after short information 
[76]. Similar simple advice also works in clinic settings 
[77,78]. One population- and one clinic-based study suggest that MOH can be successfully managed in a primary care setting after an initial collaboration with headache specialists 
[45,79].

The common headache disorders require no high-tech investigations and may therefore be diagnosed and managed by all skilled physicians. Most headaches are therefore probably best managed in primary care. Focus on MOH in primary care is therefore important both in order to prevent MOH from developing and for early diagnosis and treatment.

We have designed a BI for treatment of MOH in primary care and planned a double-blinded cluster randomized parallel controlled trial (RCT) to evaluate effects of the intervention.

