### Data handling and statistical analyses

#### Power calculations

According to the Norwegian Medical Association, the average number of listed patients pr GP is approximately 1200. Using 1000 patient pr GP (simplicity) gives us (based on previous studies 
[4,5]) an estimate of approximately 30–40 patients with chronic headaches and 10 patients with MOH per GP.

Using previous results from studies from Akershus University Hospital 
[76] regarding number of days of medication intake per month and proportion of patients with headache more than 15 days per month before and after unstructured information about MOH, we have made an approximation of the required sample size.

Using 80% power for the detection of a similar sized difference as found in the previous study for number of days of medication intake 
[76], we would need 18 patients in each arm unadjusted and five clusters (ie. GPs) with eight patients each, to achieve significant results at the 5% level. For analysis of the proportion of patients with more than 15 days of headache, power calculations yield 30 patients or eight clusters (GPs) with eight patients each. Since the intra-cluster coefficient of correlation is not known (here estimated at 0.5 as a “worst case”) and since we don’t know the degree of carry-over of information from one group of GPs to another, we assume a sample size of 20 physicians (160 patients) to be reasonably safe. This would also give significant results at the 5% level even if only five patients per GP were included.

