[80,81]. However, especially among those with chronic or co-occurring headache types, diagnosing headaches is not always easy. The gold standard for making a specific headache diagnosis is an interview combined with a physical and neurological examination by a physician experienced in headache diagnostics. All patients will be diagnosed based on interviews by a GP trained and experienced in headache diagnostics also in order to avoid inter-observer variation ([name]).

Some of our data will be based on retrospective self-reports and therefore open to recall bias, although here is no reason to suspect systematic bias. In order to counteract this, we will also use headache data from prospective headache diaries 
[87]. Recent studies using a similar headache diary with written instructions before first consultation found high usefulness, acceptability and comprehensibility of the diary as well as good compliance and completeness of data 
[105,106]. We will use the headache diary for periods of two weeks. This period may seem too short for infrequent forms of headache, but in our sample of chronic sufferers this should not be a problem. In addition, a longer headache registration period may reduce compliance and cause greater interference with the cohort.

A common finding in many brief intervention studies and RCTs on alcohol use, are small reductions in alcohol consumption at follow-up also in the control group 
[73,107]. Possible reasons for this may be motivational effects of screening, sensitization to screening/measurements/follow-up, non-intended advice also in BAU group, and “regression towards the mean”. In this study we have tried to minimize most assessment effects by doing a double-blinded parallel RCT, and the screening questionnaire about medication use for headache is embedded with other questions about headache in the very short screening questionnaire. The control group will not receive the SDS screening before the three months follow-up and will therefore not be affected by this.

The SDS has not been validated against other measurements of dependency in MOH sufferers and, indeed, there is still much discussion as to whether MOH represents dependency 
[50-55,57]. Being fully aware of this, we will use the SDS score, not as an attempt to define dependency, but rather to distinguish between chronic headache subjects with and without medication overuse 
[30,35].

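### The sample size is justified at the 5% level with an uncontrolled before–after change, but the two primary BI-versus-BAU tests are Bonferroni-corrected and headache days has no calculation of its own

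*Protocol article*

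**What the plan says.** **Level and power.** Under Power calculations, the protocol article sizes the trial as follows: "Using 80% power for the detection of a similar sized difference as found in the previous study for number of days of medication intake", 18 patients are needed in each arm unadjusted, or five GPs with eight patients each, "to achieve significant results at the 5% level". The plan then goes to 20 GPs and 160 patients, because the intra-cluster correlation (set at 0.5 as a pessimistic value) and the carry-over between GPs are unknown. It adds that five patients per GP would still suffice at 5%.

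**Source of the difference.** The same section takes its figures from results "before and after unstructured information about MOH". Under Background, the source is described as an "open, un-controlled study of medication overuse headache in the general population".

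**Second calculation.** "For analysis of the proportion of patients with more than 15 days of headache, power calculations yield 30 patients", or eight GPs with eight patients each. Outcome measures and Table 3 make the numbers of headache days and medication days primary at 3 months. Proportions without chronic headache or medication overuse are secondary.

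**Planned tests.** Under Statistics, BI and BAU are compared with mixed linear models, and the confirmatory analyses "regarding the two primary and the secondary outcomes will be performed as hypothesis testing on the entire dataset and Bonferroni corrections will be used". No divisor is given.

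**Control arm.** Under Discussion, brief-intervention trials on alcohol are said commonly to find "small reductions in alcohol consumption at follow-up also in the control group", with regression towards the mean among the possible reasons.

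**The concern.** The power statement and the analysis plan do not describe the same test, in three respects.

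1. The power is computed at 5%, but with two Bonferroni-corrected primary outcomes each is tested at 2.5% at most.
2. A within-group change after information is used as the difference between two randomised arms. The two are equal only if BAU patients do not change at all. Patients enter because they screened at 15 or more headache days and 10 or more medication days per month, a selection that invites regression towards the mean.
3. Headache days is a primary outcome without a calculation; a secondary-type proportion stands in for it.

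Significance carries real weight here. Outcome measures treats any significant improvement as relevant, and Ethics and data security makes the offer of BI to the BAU arm depend on a significant benefit at three months. The chance of reaching significance should therefore be stated for the tests that will be run.

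**Working it through.** **Inputs from the protocol article:** power 80%, level 5%, 18 per arm unadjusted, eight (or five) patients per GP, correlation 0.5, 20 GPs. **Assumptions:** two-sided tests, 10 GPs per arm, the GP as the cluster as in the plan's own calculation, and a normal approximation. The plan gives no difference or standard deviation, so the standardised difference d is back-solved.

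**Formulas.** Power = Φ(d·√(n_eff/2) − z_(1−α/2)), with n_eff = n/DE and DE = 1 + (m − 1)·ICC.

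**Step 1: reproduce the plan.** For 80% at 5% with n = 18, d·√(18/2) = 1.960 + 0.842 = 2.802, so d = 0.934. At m = 8 and ICC 0.5, DE = 1 + 7 × 0.5 = 4.5, and 18 × 4.5 = 81 per arm, or 162 in total. This is essentially the planned 160, so at the plan's own correlation clustering uses up the whole increase. The figure of five GPs with eight patients does not follow from 0.5. Read as per arm, it implies (40/18 − 1)/7 = 0.175.

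**Step 2: change only the level.** z is 1.960 at 5% and 2.241 at 2.5%.

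| Setting | n_eff per arm | Power at 5% | Power at 2.5% |
|---|---|---|---|
| 18 per arm, no clustering | 18 | 80% | 71.2% |
| 160 patients, ICC 0.5 | 80/4.5 = 17.8 | 79.5% | 70.6% |
| Five per GP (100 patients), ICC 0.5 | 50/3 = 16.7 | 76.9% | 67.5% |
| 160 patients, ICC 0.175 | 80/2.225 = 36.0 | 97.7% | 95.7% |

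For example, in the second row 0.934 × √(17.8/2) = 2.784, and Φ(2.784 − 2.241) = 0.706.

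Reaching 80% at 2.5% takes 22 per arm unadjusted. With 80 patients per arm, DE may then be at most 80/22 = 3.64, so the ICC at most (3.64 − 1)/7 = 0.38. With five per GP the limit is (50/22 − 1)/4 = 0.32.

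**Step 3: wider families, as illustration.** With 160 patients at ICC 0.5, a divisor of 4 gives 61.3% and a divisor of 10 gives 49.1%. Both divisors are assumed.

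**Step 4: change under BAU.** If BAU achieves a share f of the earlier before–after change, d becomes d(1 − f). The document does not give f. Power with 160 patients at 2.5%:

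| Assumed f | ICC 0.5 | ICC 0.175 |
|---|---|---|
| 0 | 70.6% | 95.7% |
| 10% | 60.4% | 90.7% |
| 25% | 43.9% | 76.7% |
| 50% | 19.8% | 39.7% |

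**Step 5: headache days.** No difference or standard deviation is given, directly or by implication, so no power can be computed for this outcome. The proportion does not settle it. If its 30 patients are per arm at 80% power, 160 patients at ICC 0.5 give Φ(2.802 × √(17.8/30) − 1.960) = 58% at 5%.

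**The case against.** **The 80% belongs to a minimum, not to the planned trial.** This is correct. It is attached to 18 per arm and five GPs, and no power is stated for 160 patients. If the true correlation is well below 0.5, the larger sample absorbs the correction, as the last row of step 2 shows. A reader might infer that the trial is underpowered; the document does not establish that. What stands is that, at the correlation the plan itself adopts, the extra patients pay for clustering and leave nothing for multiplicity.

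**The calculation is a two-arm one for a primary outcome.** Also correct. It is tempting to say that the 80% refers to a paired test or to an outcome the trial will not analyse. The wording for each arm and the use of medication days rule that out. Only the source of the assumed difference is before–after, and only headache days lacks a calculation.

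**The Bonferroni family is not defined.** One could count every marked cell of Table 3 and derive very low power. The text names primary and secondary outcomes together but gives no divisor and does not say that they form one family, so that count is only one literal reading. The conclusion here needs no more than a divisor of two.

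**Control-arm improvement may be small.** The Discussion reports small reductions, in alcohol trials, and describes steps to limit assessment effects. The earlier effect also followed unstructured information, so structured BI might achieve more. Both points are fair, and they are why the shares in step 4 are assumptions. But blinding does not remove regression towards the mean, and taking f as zero is an assumption too, and an unstated one.

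**The proportion is a conservative stand-in.** Dichotomising usually loses information, so this is plausible. It cannot be checked without a difference and standard deviation for headache days, and no shortfall is shown for that outcome either.

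**Conclusion.** The point holds in a limited form. The 80% at 5% is not the power of the planned primary tests. With two Bonferroni-corrected primary outcomes it is about 71% at 18 per arm, about 71% with 160 patients at a correlation of 0.5, and about 68% with five patients per GP. This assumes two-sided tests, the effect implied by 18 per arm, and no change under BAU. Power for medication days exceeds 80% at 2.5% if the correlation is below roughly 0.38 with eight patients per GP, or 0.32 with five. Any improvement under BAU lowers these figures; by how much cannot be known from the document. Power for headache days is unstated and cannot be derived. The finding is that the power is misstated, not that the sample size is shown to be too small.

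**What to change.** - Under Statistics, limit the confirmatory family to the two 3-month BI-versus-BAU outcomes, headache days and medication days, tested with Holm at an overall 5%. Its first step is at 2.5%, so power computed at 2.5% is a safe floor for each outcome.
- Keep secondary outcomes outside that family: either test them afterwards in a fixed order, or report them with unadjusted intervals.
- Under Power calculations, restate power at 2.5% separately for medication days and headache days, with the assumed difference and standard deviation of each. Do this for 160 patients and for five per GP, over a range of intra-cluster correlation up to 0.5 and a range of assumed BAU change that includes zero.
- Say that the planning difference comes from an uncontrolled before–after study.

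The sample size stays as planned. The cost is rewording and recalculation, and a stated power that looks less favourable.

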### Ethics and data security

The study has been approved by the Regional Committee for Medical Research Ethics, the Norwegian Social Science Data Services (NSD) and the Norwegian Directorate for Health.

All data will be anonymised. All participating patients and GPs must give informed, written consent. The approval of the Regional Committee for Medical Research Ethics was given based on a possibility of a cross-over from the control group to the intervention group if the main outcomes at three months show a significant beneficial effect of BI. This is to avoid a six months delay in offering effective treatment. In that case, the GPs in the BAU arm will receive the BIC and be able to perform BI on their own MOH patients.

### Pilot study

The intervention has been be tested for practicability and acceptability in a pilot study with six GPs. The pilot study did not involve a control group. Recruitment methodology and logistics were tested. Patients from the pilot study will not be included in the main study.

### Dissemination/feedback of results

After the study, feedback will be given to the involved GPs regarding the efficacy of BI and main outcomes. In addition, we aim to publish the results in international peer-reviewed scientific journals and disseminate our experiences in national medical fora.

## Discussion

There is no consensus for MOH withdrawal programmes and there is therefore a need for evidence-based and cost-effective strategies for MOH 
[36,37].

To our knowledge, this is the first double-blinded cluster-randomized controlled clinical trial for MOH in primary care.

The GPs that will be included in the present study are assumed to be representative for Norwegian GPs in general in terms of localisation (urban vs. suburban), gender and age distribution. Through the Norwegian GP list-patient system, all citizens are listed with a GP. Therefore, with a representative selection of GPs, the patient population is assumed to be reasonably population-based which will increase the external validity of our findings.

The age range of patients (18–50 years of age) has been chosen in order to target the highest number of patients with chronic headache, as the prevalence is lower in younger people and older people have a higher frequency of co-morbidities. We have chosen an upper age limit of 50 years since data from the Norwegian prescription database (NorPD) also indicate that there is an increase in the number and dosage of various relevant drugs (notably anti-hypertensives and cardiovascular drugs) at approximately 50 years of age 
[104] and we want to monitor headache medication and not the use of drugs prescribed for other illnesses.

Selection bias may occur by just including patients who are willing to cooperate in the intervention; however the same selection will take place in the control group. The selection of participating GPs are based on voluntary participation and the BIC will give them CME credits. Our GPs might therefore have a higher motivation for the BI than GPs in general, but this selection will also take place in the control group. Gains for participating GPs are: i) improvement in headache diagnostics and management ii) receiving a tool for identifying and detoxifying MOH patients.

The study group will cover the normal fee for the BI consultation for the patients, apart from this there are no economic incentives for participation either for the patients or the GPs.

Although questionnaires cannot replace an encounter with a skilled physician, single questions about migraine and tension-type headache and frequency of tension-type headache have been shown to be valid 
[80,81]. However, especially among those with chronic or co-occurring headache types, diagnosing headaches is not always easy. The gold standard for making a specific headache diagnosis is an interview combined with a physical and neurological examination by a physician experienced in headache diagnostics. All patients will be diagnosed based on interviews by a GP trained and experienced in headache diagnostics also in order to avoid inter-observer variation ([name]).

Some of our data will be based on retrospective self-reports and therefore open to recall bias, although here is no reason to suspect systematic bias. In order to counteract this, we will also use headache data from prospective headache diaries 
[87]. Recent studies using a similar headache diary with written instructions before first consultation found high usefulness, acceptability and comprehensibility of the diary as well as good compliance and completeness of data 
[105,106]. We will use the headache diary for periods of two weeks. This period may seem too short for infrequent forms of headache, but in our sample of chronic sufferers this should not be a problem. In addition, a longer headache registration period may reduce compliance and cause greater interference with the cohort.

A common finding in many brief intervention studies and RCTs on alcohol use, are small reductions in alcohol consumption at follow-up also in the control group 
[73,107]. Possible reasons for this may be motivational effects of screening, sensitization to screening/measurements/follow-up, non-intended advice also in BAU group, and “regression towards the mean”. In this study we have tried to minimize most assessment effects by doing a double-blinded parallel RCT, and the screening questionnaire about medication use for headache is embedded with other questions about headache in the very short screening questionnaire. The control group will not receive the SDS screening before the three months follow-up and will therefore not be affected by this.

The SDS has not been validated against other measurements of dependency in MOH sufferers and, indeed, there is still much discussion as to whether MOH represents dependency 
[50-55,57]. Being fully aware of this, we will use the SDS score, not as an attempt to define dependency, but rather to distinguish between chronic headache subjects with and without medication overuse 
[30,35].

A Danish study has shown that feasibility, acceptability and implementation of screening and brief intervention programs for alcohol overuse in primary care may cause more problems than they solve for some GPs because it might be problematic to incorporate a brief intervention and follow-up in a busy daily practice where many other different problems are targeted 
[108]. It is clear that if physicians, and especially GPs, are to deliver interventions in a busy daily and routine practice, it is of great importance that the interventions are feasible and considered clinically relevant. We have used knowledge and experience from a study on the epidemiology of headache in Norway 
[5,6], a prescription peer academic detailing study 
[109,110], and a pilot study to investigate some of these aspects, and used this to design the final structure and contents of both the BIC and the study to be both acceptable for patients and feasible for GPs in daily practice.

To reduce the workload for participating GPs as well as for blinding purposes, the first universal/opportunistic screening for chronic headache and probable medication overuse will be performed by the external project administration prior to the BI. Through this screening we also expect to reach possible chronic headache patients who might not be known as such by their GP. Apart from this initial screening, the study is a pragmatic trial tailored to fit into a busy situation of an everyday GP.

We suggest that strengths of this study include the design and approach with randomly assigned intervention and control groups in accordance with the CONSORT statement for RCTs 
[111].

The present project holds potentials for making a change in the focus on MOH treatment in particular, as well as the medication use for chronic headache in general. The dissemination of the results and of the BI methods to inform the Norwegian health care system will be possible because of the primary care strategy. There is a potential of reducing the suffering of MOH in a large, but so far largely neglected group of patients. Effective treatment at the GP-level, is also an advantage if it does not lead to more referrals to specialists. The principle of treatment at the lowest effective level of care, in this case in primary care, is a stated aim in the Norwegian health care system where also the geographical situation often reduces the accessibility to secondary health care services. In addition, a reduction in medication costs, improved headache status, and reduced secondary headache related costs, may lead to economical savings for society as well as benefits for the individual patients. Such effects may potentially be augmented by a greater awareness of GPs, pharmacists and society in general regarding dangers associated with indiscriminate use of pain killers for frequent headache.
